## Abstract

**Background:**

World Health Organization (WHO) adolescent HIV-testing and treatment guidelines recommend community-based interventions to support antiretroviral therapy (ART) adherence and retention in care, while acknowledging that the evidence to support this recommendation is weak. This cluster randomized controlled trial aims to evaluate the effectiveness and cost-effectiveness of a psychosocial, community-based intervention on HIV-related and psychosocial outcomes.

**Methods/design:**

We are conducting the trial in two districts. Sixteen clinics were randomized to either enhanced ART-adherence support or standard of care. Eligible individuals (HIV-positive adolescents aged 13–19 years and eligible for ART) in both arms receive ART and adherence support provided by adult counselors and nursing staff. Adolescents in the intervention arm additionally attend a monthly support group, are allocated to a designated community adolescent treatment supporter, and followed up through a short message service (SMS) and calls plus home visits. The type and frequency of contact is determined by whether the adolescent is “stable” or in need of enhanced support. Stable adolescents receive a monthly home visit plus a weekly, individualized SMS. An additional home visit is conducted if participants miss a scheduled clinic appointment or support-group meeting. Participants in need of further, enhanced, support receive bi-weekly home visits, weekly phone calls and daily SMS. Caregivers of adolescents in the intervention arm attend a caregiver support group. Trial outcomes are assessed through a clinical, behavioral and psychological assessment conducted at baseline and after 48 and 96 weeks. The primary outcome is the proportion who have died or have virological failure (viral load ≥1000 copies/ml) at 96 weeks. Secondary outcomes include virological failure at 48 weeks, retention in care (proportion of missed visits) and psychosocial outcomes at both time points. Statistical analyses will be conducted and reported in line with CONSORT guidelines for cluster randomized trials, including a flowchart.

**Discussion:**

This study provides a unique opportunity to generate evidence of the impact of the on-going Zvandiri program, for adolescents living with HIV, on virological failure and psychosocial outcomes as delivered in a real-world setting. If found to reduce rates of treatment failure, this would strengthen support for further scale-up across Zimbabwe and likely the region more widely.

**Trial registration:**

Pan African Clinical Trial Registry database, registration number PACTR201609001767322 (the Zvandiri trial). Retrospectively registered on 5 September 2016.

## Background

In sub-Saharan Africa, the number of HIV-related deaths among adolescents (aged 10–19 years) tripled between 2000 and 2014 despite decreasing among all other age groups. HIV is now the leading cause of death among this age group [1, 2]. The increase in adolescent HIV-related deaths has been attributed to poor prioritization of adolescents in national HIV plans, inadequate provision of accessible and acceptable HIV-testing, counseling and treatment services for this age group, plus a lack of tailored support for adolescents to remain in care and adhere to taking antiretroviral therapy (ART) [3–5]. Adolescents in sub-Saharan Africa have poorer ART adherence than adults [6] and are at high risk of loss to follow-up from treatment and care [7]. This supports findings among adolescents with other chronic childhood illnesses (e.g., diabetes, asthma) when medication adherence frequently becomes worse as the child becomes more independent from parental control as they enter adolescence [8].

In 2013, the World Health Organization (WHO) released the first consolidated ART prevention and treatment guidelines which recommended innovative models of ART delivery (decentralization, integration and task-shifting) [9]. In response, Zimbabwe revised its national ART guidance, released in December 2013, to simplify recommended treatment regimens for children and adolescents, hence facilitating the decentralization of pediatric HIV care to primary healthcare facilities [10]. Decentralizing pediatric HIV care has resulted in improved access and coverage, but little is known about the capacity of primary care facilities to provide effective adherence support as well as support for the broader psychosocial issues that many of these children and adolescents face [4].

A key tenet of both the WHO and Zimbabwe’s treatment guidelines is that expanded access to ART needs to be accompanied by interventions to maximize retention in care and medication adherence. Poor retention and adherence to ART leads to treatment resistance and ultimately, to treatment failure [5, 11, 12]. International guidelines recommend at least 95% adherence to ART to minimize the risk of virological failure [13–15]. A systematic review of 17 studies relating to ART programs in children and adolescents from low- and middle-income countries (LMIC) found that non-adherence was associated with a child’s socioeconomic environment, stigma, caregiver characteristics, dynamics of child-caregiver interactions, disclosure of HIV status, regimen complexity, side effects, and cost of medication [16].

The 2013 and 2015 WHO adolescent HIV-testing and treatment guidelines recommend community-based interventions to support ART adherence and retention in care, while acknowledging that the evidence to support this recommendation is weak [4, 17]. Evidence-based strategies to provide support to the growing number of adolescents receiving ART from LMIC are urgently required. Preliminary evidence suggests that the Zvandiri (“As I am”) program (http://www.africaid-zvandiri.org/) has the potential to make a significant impact on the lives of adolescents living with HIV [18].

The Zvandiri program is a model of differentiated clinical service delivery for HIV-positive children and adolescents in Zimbabwe, has been cited as a “best practice” intervention by the WHO [4], USAID, Southern African Development Community [19], and has been recommended for adaptation and regional scale-up [19]. The program uses trained and mentored community adolescent treatment supporters (CATS) to deliver structured support groups and tailored community-based adherence support coupled with counseling for the broader psychosocial issues that these young people are facing (including coming to terms with their emerging sexuality in the context of a life-threatening, sexually transmissible infection). The CATS are aged 18–23 years, living with HIV, have been identified by the healthcare facility as committed, competent and motivated to support their peers as well as adherent to ART, having completed secondary schooling and having consent from their caregivers to enroll as CATS. The Zvandiri program also includes an intervention for caregivers which focuses on enhancing their knowledge, skills and confidence of HIV and treatment literacy as well as communication and parenting through a participatory training program.

In this paper we describe the protocol for a cluster randomized controlled trial (cRCT) to evaluate the effectiveness and cost-effectiveness of the Zvandiri program on HIV-related and psychosocial outcomes.

## Methods/design

### Objectives

The trial will provide evidence on whether enhancing community-based support for adolescents on ART through the Zvandiri program will, compared with standard care:Reduce the proportion of adolescents with ART treatment failure (lack of viral suppression)Improve retention in careReduce the severity of anxiety and depressionReduce the proportion of adolescents reporting non-disclosureBe cost-effective

### Hypotheses

The primary hypothesis is that the Zvandiri program will be more effective than standard care in reducing the proportion of adolescents who have died or who are failing treatment at 96 weeks (defined as a viral load ≥ 1000 copies/ml).

The secondary hypotheses are that the Zvandiri program (1) improves virological failure at 48 weeks, (2) improves retention in care, (3) reduces psychological distress, (4) increases HIV status disclosure to sexual partners and (5) decreases perceived stigma.

### Trial setting

The trial is being conducted in two districts (Bindura and Shamva) in Mashonaland Central Province. The districts were selected in consultation with the Ministry of Health and Child Care (MoHCC). At the time of selection, it was estimated that 24,871 adolescents were living with HIV in the province and that ART coverage among children and adolescents was the lowest in Zimbabwe (estimated to be 29%). Additionally, although the Zvandiri program was being scaled-up, it had not yet been initiated in these two districts. Altogether, there are 33 healthcare facilities in the two districts. Of these, 16 with at least 20 adolescents on ART (excluding private clinics and those not yet offering pediatric HIV treatment and care services) were selected to participate.

### Trial design

The trial is a cluster randomized controlled trial (cRCT). The clinic is the unit of randomization. Sixteen clinics were randomized to either enhanced ART-adherence support through the Zvandiri program or standard of HIV care in a 1:1 allocation (Fig. 1). Adolescents aged 13–19 years were recruited. Trial outcomes are assessed through a clinical, behavioral and psychological assessment conducted at baseline and after 48 and 96 weeks.

**Fig. 1 Fig1:**
[figure not shown]
Trial overview

### Eligibility criteria

Inclusion criteria: HIV-positive adolescents, aged 13–19 years, eligible for ART (i.e., either starting or already on ART) and able to provide informed assent and their caregiver is able to provide informed consent (those aged 18 and 19 years do not need caregiver consent)Exclusion criteria: too physically or psychologically unwell or unable to give informed consent

### Interventions

#### Control arm

All eligible adolescents attending clinics allocated to the standard-care arm receive ART and adherence support as set out in the prevailing MoHCC guidelines [20]. As per MoHCC guidelines, adherence support is provided by adult counselors and nursing staff. After ART initiation, adolescents are seen monthly, with cluster of differentiation 4 (CD4) monitoring at 6-monthly intervals. Prescription refills, pill counts and participant interviews are used to measure adherence. Although routine viral-load testing was adopted by MoHCC in 2010 and scale-up began in 2012 [21], the MoHCC is currently only able to provide targeted rather than universal viral-load testing.

#### Intervention arm

All eligible adolescents attending intervention clinics will receive MoHCC standard care. In addition, one to three (ideally at least one man, one woman) trained and supported CATS are at each clinic to provide adherence counseling and support to adolescents at their clinic visits as well as on-going individualized community-based support. Each CATS supports 6–10 adolescents in their geographical location irrespective of level of Zvandiri support. CATS were recruited from the clinic in partnership with the clinic staff, or from the local support group if a group was already in place.

The CATS receive 2 weeks of MoHCC-endorsed training to equip them with counseling skills and skills in community outreach plus knowledge specific to adolescent HIV (ART and adherence, disclosure, sexual and reproductive health, psychosocial support and mental health). The training combines both theoretical and practical components, including the “shadowing” of existing CATS in Harare to acquire practical experience of providing adherence support. Training includes learning how to identify “red flags” for ill-health, adherence challenges, psychosocial distress and common mental disorders (CMDs), plus basic skills in problem solving and cognitive behavioral therapy (CBT). Training is participatory and uses case studies. All CATS attend a weekly supervision meeting at the clinic with a designated nurse and provide each other with peer-to-peer support (through a WhatsApp group and via Skype from Harare) with oversight from a professional counselor. Trial participants are allocated to a designated CATS according to their residential area and followed up through the short message service (SMS), phone calls and home visits. The type and frequency of contact is determined following assessment of their individual situation (i.e., whether they are considered “stable” or in need of enhanced support):“Stable” adolescents are those: (a) with a viral load < 1000 copies/ml and/or most recent (and within the last 6 months) CD4 count ≥ 200 cells/ml and (b) attending all scheduled clinic visits in the last 3 months assessed using the patient-held record. Stable adolescents receive a home visit once a month, plus a weekly, individualized SMS. The SMS is written and sent by the CATS and focuses on (i) motivational reminders around adherence, (ii) clinic and support group attendance and (iii) encouragement to contact the CATS in the event of any problems. An additional home visit is conducted if an adolescent misses a scheduled clinic appointment or support-group meetingAdolescents in need of enhanced support are those: (a) with a viral load ≥ 1000 copies/ml and/or CD4 count < 200 cells/ml, (b) at risk of other CMDs/with a major depressive disorder (assessment methods described below), (c) failing to attend one or more scheduled clinic visits in the last 3 months, (d) commencing ART in the past 3 months, (e) who are pregnant and (f) with other psychosocial challenges or protection issues. Adolescents in need of enhanced support receive bi-weekly home visits, plus weekly phone calls and daily SMS. During the home visit, the CATS conduct an adherence assessment and provide adherence counseling as appropriate. A community health nurse accompanies the CATS where possible. If adolescents require more than one home visit every 2 weeks (for child protection cases, depression, ill-health), these are conducted by CATS with the caregiver present

Adolescents are allocated to the appropriate intervention level at enrollment, and re-assessed at 3-monthly intervals by the CATS in conjunction with the clinic nurses. Adolescents are moved between levels of intervention support as indicated by clinic attendance and other clinical factors as outlined in Table 1.

**Table 1 Tab1:** Intervention components and levels of intervention support

Level of care	Standard Zvandiri support	Enhanced Zvandiri support
Eligibility criteria	• A viral load < 1000 copies/ml in last 6 months • CD4 count ≥ 200 cells/ml in last 6 months • Attending all scheduled clinic visits in last 3 months • Psychologically stable • Safe	• Commencing ART in past 3 months • A viral load ≥ 1000 copies/ml in the last 6 months • CD4 count < 200 cells/ml last 6 months • Pregnancy • Failing to attend ≥ 1 scheduled clinic visit(s) in last 3 months • Psychological distress • Abuse or neglect
Intervention	• Monthly support group • Monthly home visit • Weekly SMS reminder • Zvandiri Centre contact • Caregiver workshop	• Monthly support group • Bi-weekly home visits • Daily SMS reminder • Weekly phone calls • Zvandiri Centre contact • Caregiver workshop • Referral and linkages • Community outreach visits

*ART* antiretroviral therapy, *SMS* short message service

All participants at Zvandiri intervention sites are invited to attend a monthly support group, facilitated by a support-group leader (a volunteer nurse, teacher or social worker) in conjunction with the CATS, with supervision from the intervention coordinator. A standardized curriculum is used, focusing on improving health and treatment literacy, HIV disclosure, resilience and coping strategies, sexual and reproductive health, social networks and awareness of, and linkages to, services as required. Adolescents are actively followed up by the CATS to maximize attendance at this support group. Adolescents identified to be at risk of harm are immediately referred to the Zvandiri intervention coordinator or clinic nurse for mental health services and/or management with the Department of Social Services.

### Zvandiri intervention conceptual framework

The Zvandiri intervention is informed by the Unified Theory of Behavior (UTB) [22, 23]. The UTB is a validated conceptual framework that has previously been adapted to support adolescent behavior change within the context of a family centered approach. The UTB conceptualizes behavior in terms of two dimensions – the immediate determinants of behavior, and of behavioral intention. It states that adherence to ART (for example) is more likely to occur if both (1) the determinants of adhering to ART and (2) the intention to adhere to ART are “aligned in favor of its enactment” [22, 23]. The five immediate determinants of behavior (i.e., ART adherence) are shown in Fig. 2, as are the immediate determinants of behavioral intention (i.e., intention to adhere to ART). We used this framework, combined with evidence from the academic literature about the determinants of adolescent HIV adherence and data from our formative work, to develop a modular Zvandiri intervention ensuring that each component of the framework is adequately addressed.

**Fig. 2 Fig2:**
[figure not shown]
Adolescent and family centered intervention for antiretroviral therapy (ART) adherence

Caregivers of adolescents in the intervention arm are invited to a 12-session caregiver support group, facilitated by the intervention coordinator and CATS over 12 months. Sessions are in Shona, the participants’ language. The sessions focus on improving caregivers’ knowledge, skills and confidence of HIV and treatment literacy, communication and parenting and available support services. Two sessions are held jointly with adolescents.

### Definition of endline

The primary endpoint will be at 96 weeks post enrollment. There will be an 8-week window period on either side of this endpoint to allow flexibility in timing of visit (i.e., 88–104 weeks).

### Outcomes

The primary outcome is the proportion of participants who have died or who have a viral load ≥ 1000 copies/ml at 96 weeks, assessed on a dried blood-spot sample. Secondary outcomes are assessed at 48 and 96 weeks, and are the proportion of participants:Who are not retained in clinic services stratified according to the WHO definition [24]. Full retention is defined as attending > 80% of scheduled clinic appointments; partial retention as attending 30–80% of scheduled appointments and non-retention as < 30% attendance at scheduled appointments) [24]. Retention in services will be measured through attendance at scheduled clinic visits (scheduled visit defined as visit within ± 7 days of exact date)Who discontinue ART defined as completely stopping taking drugs for at least 3 months, as documented in clinic records (3 months is the minimum period associated with risk of progression to new clinical AIDS events or death) [25, 26]With depression, defined as scoring ≥ 10/27 on the Patient Health Questionnaire (PHQ-9), a scale that has been widely used in Africa [27, 28] and recently validated for use in Zimbabwe [29]With CMDs (depression and/or anxiety), defined as scoring ≥ 8/14 on the Shona Symptom Questionnaire (SSQ-14) which was developed and validated in Zimbabwe using exemplary cross-cultural methods [30]. This cut-point may be amended prior to locking the analysis plan, based on results of a separate validation study. Only two of its items relate to somatic symptoms making it useful in participants with physical disease. Severity of CMDs will also be assessed using the SSQ-14 as a continuous scoreWith poor quality of life, measured using a previously-validated Shona version of the European Quality of Life-5 Dimensions (EQ-5D) scale [31, 32]

Exploratory outcomes are assessed at 48 and 96 weeks, and are the proportion of participants:Self-reporting disclosure of HIV status to sexual partners, assessed using a self-completed questionnaireSelf-reporting perceived stigma measured using the HIV/AIDS Stigma Instrument for people living with AIDS (PLWA) (HASI-P) which has been validated in Africa [33]

### Sample size and potential power of the trial

The total sample size of 500 participants recruited from 16 clusters will provide 80% power to detect a difference in detectable viral load of 35% among participants in the standard-care arm versus 18% in the intervention arm assuming 20% loss to follow-up and a coefficient of variation (*k*) between clusters of 0.25 [34]. For secondary outcomes, the trial will have 90% power to detect, for example, a difference in non-complete attendance of 26% in the standard-care arm versus 10% in the intervention arm, and 80% power to detect a difference in mean SSQ-14 [30] score of 7.4 in the control arm and 4.8 in the intervention arm (standard deviation (SD) = 3.74).

### Study schedule

Figure 3 shows the study schedule which follows the Standard Protocol Items: Recommendations for Intervention Trials (SPIRIT) guidelines.

**Fig. 3 Fig3:**
[figure not shown]
Schedule of enrollment, interventions and assessments following the Standard Protocol Items: Recommendations for Intervention Trials (SPIRIT) guidelines

### Randomization

Imbalance between arms was minimized by using restricted randomization and matching of clusters on size and number of people in HIV care. Sixteen clusters were allocated 1:1 to either the immediate intervention or the control arm. To maximize transparency and buy-in from key stakeholders, a public randomization procedure was undertaken on 5 July 2016 involving MoHCC, Community Advisory Board members, and district-level governance and medical representatives.

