#### Quantitative data analysis

Data collected using ACASI and CAPI is downloaded into a password-protected Access database. The data will be analyzed using Stata 14. Statistical analyses will be conducted and reported in line with Consolidated Standards of Reporting Trials (CONSORT) guidelines [37] including a flowchart. Baseline characteristics of enrolled participants and the number continuing through the trial, actively withdrawing, and passively lost to follow-up will be shown by arm. The outcome measures will be summarized at baseline, 48 and 96 weeks by intervention arm, using proportions or means (SD) as appropriate.

Analyses will be intention-to-treat. Analyses will be based on cluster-level summary measures, as individual-level regression methods do not perform robustly when there are relatively few clusters per arm, especially for stratified cluster randomized trials [38]. For binary outcomes, the impact will be estimated by the risk ratio (RR) and risk difference (RD). The stratum-specific risk ratios will be estimated as the ratio of the geometric mean risks between arms for each of the two strata, and the overall RR will be estimated as the weighted-average of these stratum-specific risk ratios. An approximate variance for the log of the mean risk in each arm will be estimated from the residual mean square from a two-way analysis of variance of community log-risk on strata and study arm. A 95% confidence interval (CI) for the RR will be estimated from this variance using a stratified *t* test with 14 degrees of freedom. Similarly, a 95% CI for the RD will be estimated from an analysis of variance of the mean risk on strata and study arm. For continuous outcomes, the measure of effect will be the mean difference between arms, analyzed in an analogous method based on mean scores in each facility.

Secondary planned analyses will examine the impact of the intervention separately by age group, gender, duration on treatment, with assessment of effect-modification of the intervention effect by facility type using a previously described method [39]. Pre-defined sensitivity analyses will include adjustment for baseline viral load and other variables imbalanced at baseline. We will conduct sensitivity analyses to investigate the effect of missing data by using multiple imputation, analyzed using an individual-level Poisson regression model, allowing for within-cluster correlation using generalized estimating equations.

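### The analysis uses two strata that the randomization section does not describe, and its 14 degrees of freedom fit neither a two-strata model nor matched pairs

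*Protocol article*

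**What the plan says.** Four sections of the protocol article bear on this point.

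- **Trial design:** sixteen clinics, randomized 1:1. Neither strata nor matching is mentioned.
- **Randomization:** balance was sought through "restricted randomization and matching of clusters on size and number of people in HIV care", with the allocation drawn in public on 5 July 2016. No strata are named, and the text does not say whether matching means pairs.
- **Quantitative data analysis:** the primary analysis works on clinic-level summaries. It forms a risk ratio "for each of the two strata" and takes a weighted average of them. The variance comes from the residual of a two-way analysis of variance of log clinic risk, with stratum and arm as factors. The confidence interval then uses a t test that is called stratified but has 14 degrees of freedom. The strata are treated as already known, and matching is not mentioned.
- **Sample size and potential power of the trial:** with 500 participants, power of 80% is claimed for viral-load failure of 35% under standard care against 18% with the intervention. The calculation is made "assuming 20% loss to follow-up and a coefficient of variation (*k*) between clusters of 0.25". This section mentions neither matching nor strata.

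**The concern.** The allocation is described in terms of matching, the variance model in terms of two strata, and the degrees of freedom are those of a comparison with neither. With only 16 clinics, the grouping factor decides which between-clinic variation enters the error term and how many degrees of freedom remain, and so it shapes the primary confidence interval. If the grouping stays unclear, the choice between strata, pairs and neither could be made after outcomes are known. The 14 degrees of freedom are also an error in themselves, because the model in the same paragraph does not leave that many.

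**Working it through.** **Degrees of freedom.** Input: 16 clinics, 8 per arm (Trial design; Randomization).

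| Analysis | Calculation | df | Two-sided 5% critical t |
|---|---|---|---|
| No strata, no pairs | 16 − 2 | 14 | 2.145 |
| Two-way ANOVA, main effects, two strata | 16 − 1 − 1 − 1 | 13 | 2.160 |
| Separate arm means in each of two strata | 16 − 4 | 12 | 2.179 |
| Eight matched pairs | 8 − 1 | 7 | 2.365 |

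The stated 14 fits only the first row. The text describes the second row (the two-way ANOVA) or the third (risk ratios formed within strata). At the same standard error, the correct interval is wider by 2.160/2.145 = 1.007 (0.7%) or 2.179/2.145 = 1.016 (1.6%).

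**Stated power, reproduced first.** Inputs from the sample size section: p0 = 0.35, p1 = 0.18, k = 0.25, and 500 participants less 20% = 400, so m = 25 per clinic and c = 8 clinics per arm. A two-sided alpha of 5% is assumed. That section does not state it, but it agrees with the planned 95% interval.

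V = p0(1−p0)/m + p1(1−p1)/m + k²(p0² + p1²)
= 0.2275/25 + 0.1476/25 + 0.0625 × (0.1225 + 0.0324)
= 0.009100 + 0.005904 + 0.009681 = 0.024685

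- Unmatched formula, clinics needed per arm for 80%: 1 + 7.849 × 0.024685/0.0289 = 7.70, that is 8.
- Unmatched formula, power with 8: z = √(7 × 0.0289/0.024685) − 1.96 = 0.903, giving 81.7%. The stated 80% is reproduced.
- The two secondary figures reproduce in the same way: 91.5% for attendance (stated 90%), and 80.3% for mean SSQ-14 (stated 80%, with k = 0.25 applied to the means).

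**Power under the other designs.** Non-central t with non-centrality 0.17/√(0.024685/8) = 3.06:

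- 14 df: 81.2%
- 13 df: 80.7%
- 12 df: 80.2%
- 7 df, with within-pair k still 0.25: 74.7%

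The pair-matched formula, in which the leading 1 becomes 2, gives z = √(6 × 0.0289/0.024685) − 1.96 = 0.690, or 75.5%. That result depends on the k remaining within pairs:

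| Within-pair k | Power, matched formula |
|---|---|
| 0.15 | 86.5% |
| 0.20 | 81.6% |
| 0.25 | 75.5% |
| 0.30 | 68.7% |

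Setting power to 80% and solving: k² = (6 × 0.0289/7.849 − 0.015004)/0.1549 = 0.0458, so k is about 0.214.

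**The case against.** The strongest reply is that this is a journal article. Definitions of strata and restriction criteria commonly sit in the full protocol or analysis plan, and the trial overview figure is not shown. The randomization section never speaks of pairs. Matching could loosely mean grouping clinics into two strata by size, or the strata could be the two districts named under Trial setting, although the article does not call them strata. On either reading the stratified analysis may be the right one.

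Much of this stands. Failing to define the strata would, alone, be missing detail rather than an error. It also disposes of three stronger readings:

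- **That the analysis departs from the allocation.** A reader might infer this from the two sections. The text does not establish it, because the two strata may be the groups used in the draw.
- **That the stated power is wrong.** The 80% is correct for an unmatched comparison and survives a two-strata analysis. The drop to about 75% needs three conditions together, and the article states neither pairing nor a paired analysis.
- **That the interval should be about 10% wider.** This is only 2.365/2.145. It counts the degrees of freedom lost by pairing but assumes that pairing gains nothing in variance.

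Nor does matching oblige a pair-level analysis. Leaving effective balancing factors out of the model tends to make intervals conservative.

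The reply does not reach the degrees of freedom. The article chose to give the model terms and the number, and the two disagree.

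**Conclusion.** The point holds in a limited form. As written, the primary analysis cannot be shown to follow the allocation, because nothing connects the matching in the randomization section with the two strata in the analysis section. The 14 degrees of freedom are wrong for the stratified model described.

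If the design has two strata, the numerical error is small: 13 or 12 degrees of freedom in place of 14, an interval 0.7% to 1.6% wider at the same standard error, and power of 80.2% to 80.7%. If clinics were paired and are analysed as pairs, 7 degrees of freedom apply. Power is then about 75% if the within-pair k stays at 0.25, and 80% is kept at about 0.21 or less. These figures rest on 25 analysed participants per clinic, equal clinic sizes and a two-sided 5% level. What was actually drawn is known to the sponsor but cannot be read from the article.

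**What to change.** State in the Randomization section which groups, if any, were used in the draw of 5 July 2016. Make the primary analysis follow them, and replace the 14 degrees of freedom with the number that analysis leaves.

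- **Two strata used:** name them in the Randomization section, and use 13 degrees of freedom for the main-effects two-way analysis of variance, or 12 if arm means are estimated separately within each stratum. The 80% power statement can stay.
- **Eight pairs used and analysed as pairs:** use 7 degrees of freedom and say whether k = 0.25 refers to variation between all clinics or within pairs. Restate power if it is the within-pair value.
- **Neither used, only a restricted list of allocations:** 14 degrees of freedom are then right for the unstratified comparison, and the stratum term needs a stated basis or should go.

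The cost is a few sentences, a slightly wider interval in the stratified case and, only in the paired case, possibly a lower stated power.
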